**Methods/design:**

We will perform a randomized control trial (RCT) to evaluate the efficacy and neural mechanisms of MHRT. The sample will include 160 participants (including 120 patients with TS and 40 healthy controls). The patient sample will be randomly divided into three groups exposed to three different types of training: MHRT, HRT, and psychoeducation and supportive therapy (PST). Participants will be assessed and undergo resting-state fMRI scans at baseline and at the end of the 12-week training. The Yale Global Tic Severity Scale (YGTSS) and Premonitory Urge for Tic Scale (PUTS) will be used to assess the severity of tic symptoms and premonitory urges. The primary outcomes are change scores on the YGTSS and other assessments from baseline and the end of the training. The secondary outcomes are the neural correlates of these trainings among these groups based on graph theory, which is used to characterize brain functional connectivity networks. The default mode network (DMN) and the salience network (SN) will be assessed (which have been associated with mindfulness as well as the generation of tic symptoms) by network parameters, including clustering coefficients and shortest path lengths. Changes in these network parameters will be regarded as the neural correlates of the behavioral training.

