#### Sample size estimation

In accordance with the experimental design, three groups of participants will be included: the HRT group, MHRT group, and psychological education and supportive therapy (PST) group.

In addition, for the sample size, we use the formulas (see Supplementary Figure S1) to **calculate** the sample size (α = 0.05, 1–β = 0.8). Taking YGTSS scores as the indicator of a curative effect and based on the effect size of 0.68 calculated in a preliminary pilot test, it was calculated that at least 23 participants were needed in each group, and the drop-out rate was estimated to be 20%. Based on previous experience, 15% of MRI scans have invalid data, resulting in at least 34 subjects being required in each group (38). Therefore, 40 patients will be recruited in each group, for a total of 120 patients in this study. In addition, another 40 healthy controls will be recruited as blank controls for the behavioral and imaging research. A total of 160 participants will be included.

All evaluators will be blinded, and the treatment condition assignment will not be disclosed until after the intervention. The clinical evaluator will not be informed of which therapeutic modality the participants will receive in the evaluation process. Moreover, all dropouts must be accounted for and reported. The reasons for dropouts are mentioned. Intention-to-treat analysis was used to assess the missing data.

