#### Preprocessing

Processing steps will use MATLAB and Data Processing Assistant for Resting State fMRI (DPARSF) (53). The first five volumes will be discarded to allow the magnetization to approach a dynamic equilibrium and for the subjects to get used to the scanner noise. Data preprocessing, including slice timing, head motion correction (a least squares approach and a 6-parameter spatial transformation) and spatial normalization to the Montreal Neurological Institute (MNI) template (resampling eight voxel sizes of 3 × 3 × 3 mm), will be performed. A spatial filter of 4-mm FWHM (full-width at half maximum) will be used. Participants showing head motion above 3.5 mm of maximal translation (in any direction of x, y or z) and 1.0° of maximal rotation throughout the course of the scan will rule out subsequent statistical analysis.

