### Statistical analysis

Measures will be analyzed using IBM SPSS Statistics version 22 (IBM, Armonk, NY, United States).

First, the efficacy of MHRT will be tested using repeated measures analysis of variance (ANOVA). A 3 × 3 mixed design will be used to examine the main effects of group (MHRT, HRT or PST) as a between-subjects factor and time point as a within-subjects factor, as well as interaction effects. Second, for the imaging study, we will assess connectivity between the DMN and SN and compute the average Fisher r-to-z transformed Pearson correlations of the resting-state fMRI time-series between the nodes that belong to these resting-state networks. Pearson correlations will be used to replicate earlier functional connectivity studies. For analysis of the abovementioned neuroimaging indices, we will use univariate mixed-model analyses to assess the effects of MHRT and HRT. We will use the after-training outcomes as dependent variables, the group (MHRT, HRT, PST, and HC) as the independent variable and the baseline measure of the outcome as a covariate. We will also perform these analyses correcting for age, years of education and sex.

Measurement data will be presented as the mean ± standard deviation (x ± s). The demographic and efficacy indices of the three intervention groups before and after the intervention will be compared by multifactor analysis of variance (measurement data), and repeated measures analysis of variance and paired *t*-tests will be used for comparisons between multiple groups and before and after the intervention. In addition, we regarded at least 30% changes in YGTSS scores $\left[(\frac{\mathrm{Pr}e_{\left(YGTSS\right)}-Post_{\left(YGTSS\right)}}{\mathrm{Pr}e_{\left(YGTSS\right)}}\right)\times 100\%]$ as the clinically meaningful level.

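### The imaging mixed model is in fact an ANCOVA: it cannot use a post-training scan without a valid baseline scan unless the baseline is imputed, at a modest cost in precision

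*Protocol article*

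**What the plan says.** The Protocol article's abstract (Methods/design) has participants "undergo resting-state fMRI scans at baseline and at the end of the 12-week training", so there are two scans per child and one of them is post-training.

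The Statistical analysis section states for the imaging indices that "we will use univariate mixed-model analyses to assess the effects of MHRT and HRT". It then fixes the terms. The outcome is the post-training value only: "We will use the after-training outcomes as dependent variables". The factor has four levels, namely the three arms and the healthy controls. The first scan enters on the other side of the equation, with "the baseline measure of the outcome as a covariate". A further run adjusts for age, years of education and sex.

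Two other sections bear on how many children reach this model:
- Preprocessing sets the head-motion rule at the level of the child: "Participants showing head motion above 3.5 mm of maximal translation", together with a rotation limit, are ruled out of later analysis.
- Sample size estimation expects that "15% of MRI scans have invalid data" and that "the drop-out rate was estimated to be 20" per cent. It also names intention-to-treat for missing data, without giving a method.

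**The concern.** A mixed model earns its name from repeated outcomes within a child. Here the only repeated measurement, the baseline scan, has been moved to the covariate side. Each child contributes one row per index, and nothing is left within the child for a random effect to describe. The label suggests a tolerance of missing scans that this layout does not have.

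The practical consequence concerns children whose baseline scan is unusable but whose post-training scan is good. They have an outcome but no covariate value, so the model as specified cannot use them unless the baseline is imputed. The head-motion rule points the same way: read literally, one failed scan removes the child and not just the scan. At stake is the precision of the arm contrasts on the mechanism outcome, from scans that will already have been acquired.

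**Working it through.** **Inputs from the Protocol article (Sample size estimation).** 40 patients per arm, 20% drop-out, 15% invalid scans, a stated minimum of 23 evaluable per group, and 34 per group after losses.

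**Assumptions, not in the document.** The 15% applies at each visit. The correlation φ between failure at baseline and failure post-training runs from 0 to 1. The baseline–post correlation ρ of an index is 0.3 to 0.7.

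**The plan's own figure.** 23 / (0.80 × 0.85) = 33.8, rounded up to 34. This reproduces and shows that the 15% was applied once, although the model needs two valid scans. How 23 itself was obtained does not affect this point.

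**Scans and pairs per arm of 40.**
- Valid post-training scans: 40 × 0.80 × 0.85 = 27.2.
- Complete pairs, independent failures: 27.2 × 0.85 = 23.1.
- Valid post-training scans without a baseline: 27.2 − 23.1 = 4.1, or 15% of the valid post-training scans.

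**With correlated failures.** Scans lost = 40 × 0.80 × 0.15 × 0.85 × (1 − φ) = 4.08 × (1 − φ). Complete pairs = 27.2 minus that.

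**Precision.** With n_p pairs and n_u post-only children per arm, and unit variance, the information on an arm's post-training mean is n_p/(1 − ρ²) from the pairs. A two-scan model with a common baseline mean adds n_u. The relative gain is n_u(1 − ρ²)/n_p, and the standard error falls by 1 − 1/√(1 + gain).

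| φ | Lost | Pairs | Information gain at ρ = 0.3 / 0.5 / 0.7 | Standard error reduction |
|---|---|---|---|---|
| 0 | 4.1 | 23.1 | 16.1% / 13.2% / 9.0% | 7.2% / 6.0% / 4.2% |
| 0.25 | 3.1 | 24.1 | 11.5% / 9.5% / 6.5% | 5.3% / 4.4% / 3.1% |
| 0.5 | 2.0 | 25.2 | 7.4% / 6.1% / 4.1% | 3.5% / 2.9% / 2.0% |
| 0.75 | 1.0 | 26.2 | 3.5% / 2.9% / 2.0% | 1.7% / 1.4% / 1.0% |
| 1 | 0 | 27.2 | 0 | 0 |

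**Check by simulation.** The formula treats the covariance as known. With the covariance estimated and independent failures, two simulation runs (2,000 and 3,000 trials per correlation) gave standard errors smaller by 7.5% and 7.9% at ρ = 0.3, by 6.8% and 6.7% at ρ = 0.5, and by 4.3% in both at ρ = 0.7. In information terms that is about 9% to 18%, so the need to estimate the covariance does not remove the gain.

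**Alternative reading of the 15%.** Suppose it is the share of children with any invalid scan, split equally between visits. Then 40 × 0.80 × 0.075 = 2.4 post-training scans per arm lack a baseline, against 40 × 0.80 × 0.85 = 27.2 pairs. The gain is 2.4 × (1 − ρ²)/27.2, about 8.0% to 4.5%, and the standard error falls by about 4% to 2%.

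**The case against.** The strongest reply is that baseline-adjusted ANCOVA is a standard, valid analysis of a randomised two-scan design, and that imputing a missing baseline would keep these children without replacing the model. Both statements are right. The case for the two-scan model is that it uses the same data without an imputation step and matches the label the plan already uses.

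Three stronger readings are tempting, and the document does not support them.

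- *A valid post-training scan is discarded whenever the baseline scan failed.* The article does not say this. It says nothing about a missing covariate beyond naming intention-to-treat, and that detail is commonly left to an analysis plan, which is not shown. In the Preprocessing rule, the word for participants may be loose wording for a per-scan exclusion, since the sentence speaks of motion over the course of the scan.
- *Restricting to children who kept still twice biases the comparison of arms.* The baseline scan precedes training, so its failure cannot be caused by the training received. Excluding those children costs precision and narrows the population, but does not by itself bias MHRT against HRT. Failure of the post-training scan could relate to arm, but then neither model has that outcome. Nor does the article attribute its 15% to movement.
- *The imaging analysis falls below its planned size.* Even with independent failures, 23.1 complete pairs per arm meet the stated minimum of 23. That minimum was set for the YGTSS and not for imaging. Recruiting only 34 would have left 34 × 0.80 × 0.85 × 0.85 = 19.7, but the plan recruits 40.

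If movement does drive scan failure, the same children will tend to fail twice. The loss then lies nearer the lower rows of the table than the top one.

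**Conclusion.** The point holds as one of efficiency and labelling. The model specified is an ANCOVA, and it cannot use a valid post-training scan when the baseline scan is invalid, unless the baseline is imputed. On the plan's loss rates, taken per visit, this concerns at most about 4 of 27.2 valid post-training scans per arm, about 2 at a failure correlation of 0.5, and none if failures coincide completely. Using both scans would shorten the standard error of an arm contrast by about 4–8% (9–18% more information) under independent failures, and by about 2–4% under moderate correlation, for ρ from 0.7 to 0.3. Neither ρ nor the failure correlation is given in the article, so these are ranges under stated assumptions. The planned analysis remains valid and no bias between arms is shown. Severity is minor, because the imaging indices are secondary outcomes.

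**What to change.** **Statistical analysis section.** For the three randomised arms, replace the imaging model with one linear mixed model per index that takes both scans as outcomes. Specify an unstructured 2 × 2 within-child covariance, a baseline mean common to the three arms, visit, arm-by-visit, and a small-sample degrees-of-freedom correction. Read the MHRT–HRT contrast at the post-training visit. The planned run adjusted for age, years of education and sex can be kept.

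**Healthy controls.** They are not randomised, so the common baseline mean must not extend to them. Keep the planned comparison either by giving this group its own baseline mean in the model or by analysing it separately.

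**Preprocessing section.** Word the head-motion rule so that a failed scan is removed and the child's other scan stays. Without this, changing the model recovers nothing for children lost through motion.

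**Cost.** A few sentences and slightly more complex model syntax in the software already named, with no additional data. The model needs the degrees-of-freedom correction and rests on a missing-at-random assumption, which should be stated. If the sponsor prefers to keep the ANCOVA, the lesser change is to call it that and say how a missing baseline index is handled.

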Some theoretical understandings of the brain mechanisms involved in mindfulness take their lead from considerations about the roles of the major brain networks and their interplay (21). Functional connectivity in intrinsic brain networks, which include the salience network (SN), default mode network (DMN) and central executive network (CEN), has been suggested to be important in the networks prominently involved in cognition and mindfulness (26, 27). Mindfulness training involves participants training the attention system to inhibit irrelevant sensory stimuli and enhance relevant sensory stimuli (28) and consists of focusing attention on physical sensations (29). This suggests that mindfulness can improve the patient's perception of PUs. Mindfulness-mediated decreased connectivity between the cuneus and SN may be related to self-awareness (27). The primary node of the SN is within the anterior insular cortex (30). Neuroimaging studies have suggested that PUs are associated with the insula and anterior cingulate cortex (ACC) (31, 32). A review indicated that mindfulness-based treatments may be effective in restoring connectivity between the DMN and the CEN and SN in individuals with PTSD (33). Meditation practitioners showed significantly stronger connectivity between the DMN and SN (34), as well as increased connectivity in systems important for emotion and reward (35). This may explain why mindfulness reduces anxiety and depression and enhances wellbeing. On the other hand, TS patients exhibited a reduction in serial information transfer within the DMN and SN (36). TD patients benefit from increased functional connectivity within the DMN as a compensatory function (37). From the perspective of brain networks, we speculate that mindfulness can provide useful support for conventional HRT in TS patients. To understand the underlying mechanisms of mindfulness in TS, we will focus on two key brain networks, the DMN and SN.

Therefore, this project plans to carry out an RCT of MHRT in the treatment of TS, further systematically verify its efficacy and explore the brain mechanisms underlying the synergy of MHRT. The significance and value of this study are to form a suitable psychological and behavioral intervention scheme for TS, resolve the dilemmas in clinical treatment to a certain extent, and provide data for further clarifying the pathophysiological mechanisms underlying TS.

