## Methods/design

### Participants

#### Recruitment of participants

Recruitment of TS patients will be from the Department of Psychiatry, Beijing Children's Hospital, where participants will have received a diagnosis of TS from an experienced multidisciplinary team including at least two attending psychiatrists using the diagnostic criteria in the DSM-5. The inclusion criteria were as follows: (1) 7–12 years old; (2) Chinese children's Wechsler intelligence test IQ ≥ 80; (3) first onset with no previous treatment; and (4) right-handed. The exclusion criteria were as follows: (1) diagnosed with other mental disorders, apart from obsessive–compulsive disorder (OCD) or attention deficit hyperactivity disorder (ADHD); (2) diagnosed with epilepsy or other neurological diseases (including craniocerebral trauma); (3) claustrophobia; and (4) metallic foreign objects in the body. The recruitment period was predefined for one and a half years (May 2022 to Dec 2023).

Recruitment of healthy controls will be from a primary school in Beijing. The inclusion criteria were as follows: (1) aged 7–12 years; (2) IQ ≥ 80; and (3) right-handed. The exclusion criteria were as follows: (1) diagnosed with neurological or mental diseases; (2) claustrophobia; and (3) metallic foreign objects in the body.

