The mechanisms underlying mindfulness mainly involve two brain networks: the DMN and SN (26, 63, 64). The insula and anterior cingulate, which are responsible for premonitory impulses, are the key nodes in the SN network, and this network is dysfunctional in those with TS (31, 32, 65). Research shows that the main function of this network is to screen internal and external “key stimuli” (22, 63). We speculate that with the integration of mindfulness training technology, the first improvement with MHRT is enhancing the brain functional connections of the network such that the neural signals of PUs can be more easily “screened”. The default network is more closely related to “self”-related processing, and mindfulness training can improve an individual's self-awareness (66). Therefore, improved brain function involving the default network may improve the ability to detect PUs. In addition, the relief provided by mindfulness for the emotions associated with anxiety will also contribute to the awareness of PUs.

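### The baseline-adjusted imaging model includes non-randomised healthy controls in its group factor, so the four-group test and every healthy-control contrast can be significant with no training effect

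*Protocol article*

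**What the plan says.** In the protocol article, the imaging paragraph of Statistical analysis gives the purpose of the model: "we will use univariate mixed-model analyses to assess the effects of MHRT and HRT". The response is the post-training value ("We will use the after-training outcomes as dependent variables"), and the predictors are "the group (MHRT, HRT, PST, and HC) as the independent variable and the baseline measure of the outcome as a covariate". A further version adds demographic covariates: "We will also perform these analyses correcting for age, years of education and sex".

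The fourth level of the group factor does not come from the randomisation. Recruitment of participants states: "Recruitment of healthy controls will be from a primary school in Beijing". Sample size estimation describes their role: "another 40 healthy controls will be recruited as blank controls for the behavioral and imaging research".

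The article also expects these networks to differ by diagnosis before any training. The Introduction reports that "TS patients exhibited a reduction in serial information transfer within the DMN and SN", and the Discussion says of the salience network that "this network is dysfunctional in those with TS".

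By contrast, the clinical efficacy model in the same section is a 3 × 3 design with MHRT, HRT and PST only.

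**The concern.** Adjusting a post-treatment value for its baseline is sound for randomised arms, because they share one expected baseline and any observed imbalance is chance. It is not sound across groups that differ systematically at baseline. The adjustment compares a patient and a healthy child with the same observed baseline, but at the second scan each is expected to move back towards the mean of their own group. Those means differ, so an adjusted difference appears although nothing has changed. This is Lord's paradox.

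The neural correlates of training are the trial's secondary outcome. If the four-level group effect, or a contrast of a trained arm with HC, is read as evidence of training, a stable difference between diagnoses can be reported as a neural effect of therapy. Age, years of education and sex do not remove a difference that comes from diagnosis.

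**Working it through.** **Inputs from the article**
- Recruited: 40 per patient arm and 40 HC (Sample size estimation).
- Losses: 20% dropout and 15% invalid scans (same section). The article's own inflation reproduces with these as multiplicative factors: 23 / (0.80 × 0.85) = 33.8, rounded up to 34.
- Significance level for global graph measures: 0.05 (Statistical analysis).

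**Assumed, because the article gives no value**
- δ: baseline gap between HC and patients, in within-group SD.
- ρ: scan-rescan correlation within group.
- Evaluable patients per arm: 40 × 0.80 × 0.85 = 27.2, taken as 27.
- Evaluable HC: 40 × 0.85 = 34, assuming no dropout among them.

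**Size of the spurious difference.** Suppose no group changes. Each group keeps its own mean at both scans, with equal variances. The within-group slope of post on baseline is then ρ, and

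adjusted HC − patient difference = (post gap) − ρ × (baseline gap) = δ − ρδ = δ(1−ρ).

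It is zero only if δ = 0 or ρ = 1. Examples:
- δ = 0.3, ρ = 0.7: 0.3 × 0.3 = 0.09 SD
- δ = 0.5, ρ = 0.5: 0.5 × 0.5 = 0.25 SD
- δ = 0.8, ρ = 0.3: 0.8 × 0.7 = 0.56 SD

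Among the three randomised arms the expected baseline gap is zero, so the same formula gives zero.

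**Null rejection of the four-group test.** Simulated trials with no change in any group, 27 per patient arm and 34 HC, tested at 0.05 (1,500 trials per cell):

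| δ | ρ = 0.3 | ρ = 0.5 | ρ = 0.7 |
|---|---|---|---|
| 0.3 | 0.125 | 0.103 | 0.069 |
| 0.5 | 0.256 | 0.184 | 0.118 |
| 0.8 | 0.601 | 0.397 | 0.215 |

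A separate simulation of the same setting gave 8–57% over this grid, 17% at δ = ρ = 0.5 and about 5% at δ = 0. The two runs agree to within a few points, so only the rough range should be used.

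**Equal groups, separate simulation.** 2,500 trials per setting, δ 0.2 to 0.8, ρ 0.4 to 0.8:

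| Test | 27 per group | 40 per group |
|---|---|---|
| Four-group test | 0.058–0.422 | 0.059–0.582 |
| HC versus pooled patients | 0.061–0.590 | 0.067–0.764 |
| MHRT, HRT, PST (2 df, same model) | 0.044–0.053 | 0.047–0.059 |
| Four-group test on change scores | 0.038–0.058 | 0.043–0.056 |

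At δ = 0 the four-group test returned to 0.044–0.055, so the excess comes from the baseline gap. The mean adjusted HC-patient difference matched δ(1−ρ); for example, at 40 per group, δ = 0.5 and ρ = 0.6 it was 0.200 against 0.5 × 0.4 = 0.20.

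**The case against.** The strongest reply is that the model is meant to assess MHRT and HRT, and that those effects rest on contrasts among randomised arms, which HC do not bias. This stands. A reader might infer that the whole imaging analysis is invalid, or that the MHRT-HRT and MHRT-PST contrasts are distorted. The article does not support that: given randomisation and a common baseline slope, those contrasts keep their level in the model as written. Nor does the article say that the omnibus test is the decision rule or that HC contrasts will be read as training effects; such detail may sit in an analysis plan that is not shown. Yet the article does fix a four-level factor for the stated purpose and does not set HC apart, so the hazard is in the text.

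A reader might also infer that HC have no second scan and so cannot be in the model at all. The Abstract points the other way: it counts 160 participants including the 40 HC, and says that participants are scanned at baseline and at the end of training. The participant-flow figure is not available to settle it, so this is not part of the point.

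The objection that the size rests on assumptions also stands. The expected gap is stated only in words, and no gap is given for degree, efficiency, clustering or path length. For an index with a small gap or high reliability the inflation is minor: 6–9% at δ = 0.2 with 40 per group.

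**Conclusion.** The point holds for the four-group test and for every contrast that involves HC, and only for those. As written, they contain a component δ(1−ρ) that is unrelated to training. The mechanism follows from the model together with the article's own premise that the networks differ before training. The size does not: the roughly 8–57% null rejection (about 17% at δ = ρ = 0.5) depends on assumed δ of 0.3–0.8 SD, ρ of 0.3–0.7, 27 evaluable patients per arm and 34 HC, stable group means and a test at 0.05.

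This should be fixed before analysis, but it does not threaten the trial's main conclusion. The affected outcome is secondary, the randomised imaging contrasts remain valid, and HC do not enter the clinical efficacy model.

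**What to change.** Base the imaging training-effect test on MHRT, HRT and PST only. Two routes serve:
- drop HC from the baseline-adjusted model; or
- keep the four-group model, but pre-specify the 2-df test of the three randomised arms and its pairwise contrasts as the training-effect test, and state that the four-group test and the HC contrasts are not evidence of training.

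Use HC for the baseline comparison of patients with healthy children and, separately, for a descriptive comparison of change from baseline (time × group, without baseline adjustment). It stays descriptive because HC are not randomised.

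The cost is a change of wording, with no new data, visits or participants. Dropping HC reduces residual degrees of freedom: with the evaluable numbers assumed above, before demographic covariates, from (3 × 27 + 34) − 5 = 110 to (3 × 27) − 4 = 77, a slight loss of precision. The second route avoids even that.

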#### Construction of the network

The template of the neuroimaging research laboratory of Stanford University (Functional Imaging in Neuropsychiatric Disorders Lab website; http://findlab.stanford.edu/functional_ROIs.html) will be used to explore the DMN and SN (54). For the ROIs of the DMN and SN, see Supplementary Tables S1, S2.

We will use the Brain Connectivity Toolbox to extract the connection information between various brain regions and draw the connection diagram at the macro level. This will be used to quantitatively describe the structure, function, connection model and topological characteristics of the human brain network. We will mainly focus on the brain regions related to PUs: the insula, ACC, supplementary motor area (SMA) and prefrontal cortex. We will take the DMN and SN as the main brain function networks to consider.

Degree, global efficiency, local efficiency, path lengths and cluster coefficients will be used to investigate the relationships between the changes in these two brain functional networks and the improvements in tics and PUs and to clarify the possible brain mechanisms underlying the effects of MHRT from the perspective of brain functional networks. We will assess global network integration, segregation and connectivity between modules using the following measures for the DMN and SN: (1) degree: number of edges connected to a node; (2) global efficiency: global transmission capacity of the network; (3) cluster coefficient: degree of network collectivization; (4) local efficiency: nodal connections to within-network nodes; (5) path length: optimal path from one node to another. To assess the reliability of the results and enhance comparability with previous research, exploratory analyses on the absolute Fisher r-to-z transformed Pearson correlation connectivity matrices will be performed using the same graph indices. The calculation formulas for these parameters are presented in Supplementary Figure S2.

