For the analysis of global graph measures, we consider a significance level of α = 0.05 significant. To correct for multiple comparisons in subnetwork analyses, we will use a D/AP-Sidak adjustment that considers the mutual correlation between outcome measures (https://www.quantitativeskills.com/sisa/calculations/bonhlp.htm). For between-network connectivity analyses, we will compute an α corrected for three comparisons, i.e., adjusted for the correlation (*r* = 0.544) between the three indices after training (αBN = 0.031). For subnetwork graph analyses, we will compute a separate α for each graph measure adjusted for the correlation between the respective subnetwork measures at baseline (rFPN = 0.387, αFPN = 0.026; rDMN = 0.408, αDMN = 0.026; rSN = 0.413, αSN = 0.027).

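### Global graph measures are judged at an unadjusted 0.05, with neither their number nor a leading measure fixed, although the same paragraph adjusts the other network tests

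*Protocol article*

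**What the plan says.** The last paragraph of Statistical analysis in the protocol article sets three rules for the network tests.

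- Global measures: "For the analysis of global graph measures, we consider a significance level of α = 0.05 significant". No adjustment is stated.
- Between-network connectivity: a level adjusted for three comparisons, with a correlation of 0.544, giving 0.031.
- Subnetwork graph measures: "To correct for multiple comparisons in subnetwork analyses, we will use a D/AP-Sidak adjustment that considers the mutual correlation between outcome measures". On how that is done: "we will compute a separate α for each graph measure adjusted for the correlation between the respective subnetwork measures at baseline". The values given are "rFPN = 0.387, αFPN = 0.026; rDMN = 0.408, αDMN = 0.026; rSN = 0.413, αSN = 0.027".

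The measures are listed under Construction of the network: "Degree, global efficiency, local efficiency, path lengths and cluster coefficients will be used to investigate the relationships". They are introduced with "We will assess global network integration, segregation and connectivity between modules using the following measures for the DMN and SN". The Abstract makes the network parameters secondary outcomes, names clustering coefficients and shortest path lengths among them, and treats their changes as the neural correlates of training. The exploratory label is used only for the repeat analysis on absolute correlation matrices.

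**The concern.** Two of the three families of network tests have their significance level lowered because several correlated indices are tested. The third, the global measures, does not, and no reason is given. Each imaging index has its own univariate model, no global measure is named as leading, and the results are not labelled exploratory. Any one of the global measures that falls below 0.05 could therefore be reported as the network effect of training.

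At stake is the strength of the secondary, mechanistic conclusion about which network property changes with MHRT.

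The text also leaves unclear where the global family ends. The five measures are said to assess global integration and segregation, yet they are computed for the DMN and SN, the subnetworks that receive adjusted levels. As worded, path length in the DMN could be judged at 0.05 as a global measure or at about 0.026 as a subnetwork measure.

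**Working it through.** **Inputs**

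- Level per global test: 0.05 (Statistical analysis).
- Number of global tests, k: not given. Range used: 2 (the Abstract names two parameters), 3 (as in the plan's other families, see step 1) and 5 (Construction of the network).
- Correlation among the global measures, r: not given. Assumed range 0.387 to 0.544, the values that the document quotes for its other families, with 0 to 0.95 as sensitivity.

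**Step 1. Reproduce the plan's adjusted levels.** The D/AP-Sidak level is 1 − 0.95^(1/k^(1−r)). With k = 3:

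- between-network, r = 0.544: 0.0306 (stated 0.031)
- FPN, r = 0.387: 0.0258 (stated 0.026)
- DMN, r = 0.408: 0.0264 (stated 0.026)
- SN, r = 0.413: 0.0266 (stated 0.027)

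All four agree after rounding. With k = 2, 4 or 5 they do not; for r = 0.544 these give 0.0367, 0.0269 and 0.0243.

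**Step 2. Familywise error at 0.05 per test, independent tests.** 1 − 0.95^k:

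- k = 2: 1 − 0.9025 = 0.0975
- k = 3: 1 − 0.8574 = 0.1426
- k = 5: 1 − 0.7738 = 0.2262

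**Step 3. The same with correlated tests.** Two calculations were made: a simulation of k equally correlated two-sided z tests (400,000 runs), and the D/AP formula turned round, 1 − 0.95^(k^(1−r)). For k = 5 the exponent is 5^0.613 = 2.68 at r = 0.387 and 5^0.456 = 2.08 at r = 0.544.

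| k | Independent | Simulated, r = 0.387 | Simulated, r = 0.544 | D/AP, r = 0.387 | D/AP, r = 0.544 |
|---|---|---|---|---|---|
| 2 | 9.75% | 9.4% | 9.0% | 7.5% | 6.8% |
| 3 | 14.3% | 13.2% | 12.3% | 9.6% | 8.1% |
| 5 | 22.6% | 19.9% | 17.6% | 12.9% | 10.1% |

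Simulated F tests for k = 5, with 34 per group and 20,000 runs, agree with the z tests: 20.5% and 18.6% for three groups, 20.5% and 17.9% for four. At higher correlations the simulated z figure for k = 5 falls to 10.2% (r = 0.9) and 8.6% (r = 0.95). The D/AP figures lie below the simulated ones because k^(1−r) is a rule of thumb for the effective number of tests, not an exact joint probability.

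**Step 4. Level per test if the D/AP-Sidak rule were applied to five global measures.** 1 − 0.95^(1/2.68) = 0.0189 at r = 0.387, and 1 − 0.95^(1/2.08) = 0.0243 at r = 0.544. With r = 0 it is 0.0102. Holm would start at 0.05/5 = 0.010.

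**The case against.** The strongest defence is that the plan never says that five measures are tested globally. They are computed for the DMN and SN, and one of them is defined within a network: "local efficiency: nodal connections to within-network nodes". With two global tests the familywise error cannot exceed 9.75%, the independent case, for equally correlated tests of the kind simulated here. This stands, and it is why the size can only be given as a range.

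A second defence is that the plan's correction, as worded, runs across subnetworks within one graph measure. A global measure then has a single test, and 0.05 is what the rule itself gives. This is a possible reading but not a secure one. The stated levels are labelled by subnetwork (FPN, DMN, SN), which fits correction across three measures within each subnetwork. On that reading, exempting the global measures is inconsistent. Neither reading yields five comparisons, so k = 5 is an upper case and not the plan's own count.

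Third, 0.05 is a per-test level, the plan claims no familywise 5% for this family, and multiplicity among secondary mechanistic outcomes is often left to an analysis plan. The inflation is indeed relative to an implied target. But the article does not leave the matter open: it fixes the unadjusted level, beside two families that it adjusts.

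A reader might go further and count ten uncorrected tests, five measures in each of the DMN and SN. The document does not support this, because tests within those networks are the subnetwork tests that it adjusts. A reader might also infer that comparisons among the four groups multiply the error. The imaging models use group as one four-level variable, no pairwise imaging contrasts are specified, and the omnibus F tests above give nearly the same error as single z tests.

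**Conclusion.** The concern holds in a limited form. The plan fixes an unadjusted 0.05 for global graph measures, states neither how many there are nor which leads, and adjusts the neighbouring families. The chance of at least one false global finding is about 10%, 14% or 23% for two, three or five independent tests. For five tests at assumed correlations of 0.39 to 0.54 it is about 18 to 20% by simulation, or 10 to 13% by the D/AP formula. These correlations are borrowed from the plan's other families; a higher correlation lowers the figures.

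A single inflation factor should not be read into this, because it would need a count and a correlation that the document does not give. Nor does the point touch the efficacy conclusion on the YGTSS, which does not depend on the network tests. It is an inexpensive improvement to a secondary family.

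**What to change.** State which graph measures are tested globally, as distinct from within the DMN or SN. Then choose one of two routes before the post-training imaging data are analysed by group:

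- Adjust across the global measures, by Holm or by the D/AP-Sidak rule with the correlation taken from this trial's own blinded baseline data. For five measures the D/AP-Sidak level would be about 0.019 to 0.024 per test at the assumed correlations. Holm controls the familywise error whatever the correlation; D/AP-Sidak is more lenient.
- Name one leading global measure, tested at 0.05, and label the others exploratory.

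Either route takes one or two sentences and no new data. The cost is some loss of power for individual global measures under the first route, and a weaker claim for the non-leading measures under the second.
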